**Inclusion criteria**

- Registered clinical staff with valid licenses from the relevant regulatory bodies in Ghana. They may include Doctors, Physician assistants, Pharmacists, Nurses or Midwives
- Registered staff providing antiretroviral services to clients or working at the outpatient department of the health facility
- Aged 18 years or over
- Must have practical post-qualification experience of at least one year.

**Exclusion criteria**

- Does not consent to part take in the study

1. **Sample size**

Francis and colleagues recommended that at least 25 participants be included in any elicitation phase of research using an open-ended questionnaire(Francis et al., 2004). With an anticipated 50% response rate as observed in a similar study (2), at least 50 participants will be enrolled in this elicitation study.

1. **Elicitation Of Behavioral, Normative And Control Beliefs**

As recommended in the manual for constructing questionnaires based on the theory of planned behavior(Francis et al., 2004) and adapted for this study, the questions to be used to elicit the health workers’ behavioral, normative, and control beliefs can be found in the appendix.

1. **Analysis**

Two individuals, including the PI, will analyze the content of the responses by developing themes, labelling them and listing them in order of frequency. The most frequently reported beliefs, described as the modal set, will be used to develop the instrument to measure the health workers’ behavioural, normative, and control beliefs. As recommended, at least 75% of all beliefs listed will be included in the tool to cover the belief’ population” adequately.

#### **3.2.4 Formatting the Questionnaire**

A draft questionnaire will be developed based on the manual for constructing questionnaires based on the theory of planned behavior(Francis et al., 2004) using responses from the elicitation study. As Francis(1) recommended, the final questionnaire will contain a minimum of 40 carefully worded items across the seven theory of planned behavior domains and eight demographic items.

#### **3.2.5 Assessment of Validity and Reliability**

Five respondents will be asked to complete the draft questionnaire to help provide feedback on the ambiguity or difficulty of the questions, the length, wording or formatting of the questionnaire and inconsistency of responses. In addition, comments from experts, consultants and researchers in clinical practice and behavioural sciences on the draft questionnaire will be used to determine the construct validity of the tool. The reliability of the questionnaire will be ascertained by determining its internal consistency (Cronbach’s coefficient alpha) using STATA version 16.

### **3.2.6 TPB-Based Survey among Health Workers**

#### **a. Study Setting**

The survey will be conducted among health workers in the top 20 ART sites in the Greater Accra Region with the highest Adolescent HIV client load. According to the National AIDS Control Programme, these were the facilities as of December 2021:

- Tema General Hospital
- International Health Care Centre
- Ussher Polyclinic
- Ga South Municipal Hospital
- Ridge Regional Hospital
- Princess Marie Louis Hospital
- Ashaiman Polyclinic
- LEKMA Hospital
- Kaneshie Polyclinic
- Ga West Municipal Hospital
- Mamprobi Polyclinic
- 37 Military Hospital
- Achimota Hospital
- Madina Polyclinic(Kekele)
- Maamobi General Hospital
- Tema Polyclinic
- Adabraka Polyclinic
- Legon Hospital
- Pantang Hospital
- Amanfro Health Centre

#### **b. Sampling**

In each facility, participants will be randomly selected from eligible healthcare workers using labelled papers( Yes/No) in an opaque envelope. Those who select yes will be eligible for inclusion. Prior to the balloting, prospective participants selection will be based on the following inclusion and exclusion criteria**:**

**Inclusion criteria**

- Registered clinical staff with valid licenses from the relevant regulatory bodies in Ghana. They may include Doctors, Physician assistants, Pharmacists, Nurses or Midwives
- Registered staff providing antiretroviral services to clients or working at the outpatient department of the health facility
- Aged 18 years or over
- Must have practical post-qualification experience of at least one year.

**Exclusion criteria**

- Does not consent to part take in the study

#### **c. Sample Size**

This survey includes seven TPB variables. To detect a medium effect size of 0.15 with a power of 80% and alpha of 0.05 as Yami(2) did, a power analysis using STATA version 16 gave a minimum sample size of 89 respondents. With an anticipated 50% response rate as found in a previous study(Yami, 2015), at least 180 respondents will be invited to participate in the survey.

#### **d. Recruitment**

The administrators of prospective facilities will be engaged to seek their consent for facility participation. The study will be introduced to healthcare workers in the consenting facilities by the PI during their weekly clinical meetings. An anonymous questionnaire pack with an invitation letter and consent form will be left with the heads of relevant clinical units in the health facilities so they support and encourage the participation of their team members. A drop box will be left at the administration of each facility for completed questionnaires to be dropped in. Weekly reminders will be provided to all prospective respondents to ensure they respond within the survey period. For participants who would like to respond electronically, the link to a google form containing the questionnaire will be shared with them for completion.

#### **e. Data collection**

Data collection will be done using the close-ended self-completion questionnaire developed during phase one of the study. Printed copies and an electronic form of the questionnaire will be available. Data collection will be done within eight weeks.

#### **f. Data analysis**

Data will be exported into STATA version 16 for analysis. Descriptive statistics (frequencies and percentages) will be used to present demographic variables and participants’ characteristics. The internal consistencies of each TPB construct in the questionnaire will be verified by calculating Cronbach’s alpha. To determine the strength of relationships among all variables, correlation coefficients will be employed. Multiple regression analysis will be used to determine the extent to which the attitudes, subjective norms and PBC variables (independent variables) can predict healthcare workers’ intentions to comply with the guidelines for screening and management of hypertension among adolescents living with HIV.

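### The health-worker survey samples staff within 20 facilities, but its stated regression has no facility term, so standard errors will be too small for any TPB score that is partly shared within a facility

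*Protocol*

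**What the plan says.** All of this is in the protocol, section 3.2.6.

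- **Setting (a):** "The survey will be conducted among health workers in the top 20 ART sites in the Greater Accra Region". The sites are listed by name.
- **Sampling (b):** "In each facility, participants will be randomly selected from eligible healthcare workers", by ballot. Respondents are therefore nested in facilities by design.
- **Sample size (c):** "This survey includes seven TPB variables". The aim is "To detect a medium effect size of 0.15 with a power of 80% and alpha of 0.05", which gives "a minimum sample size of 89 respondents". At a 50% response rate, at least 180 staff are to be invited. No design effect is applied.
- **Recruitment (d):** "An anonymous questionnaire pack" is left with unit heads. Completed forms go into a drop box at each facility, or staff answer through a link to an online form.
- **Analysis (f):** correlation coefficients, then "Multiple regression analysis will be used to determine the extent to which the attitudes, subjective norms and PBC variables (independent variables) can predict" healthcare workers' intention to comply. Facility is not mentioned.

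The general analysis section (3.4.2) also names no method for clustered data. The protocol does recognise facility clustering in the trial, where section 3.3.5 uses an ICC of 0.05 for adolescents.

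**The concern.** A regression that treats all respondents as independent understates the standard error of a slope when two things hold together. Colleagues in one facility must resemble each other on the predictor, and they must also resemble each other on the part of intention that the model leaves unexplained. If either correlation is zero, nothing is lost.

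The protocol gives reason to expect some sharing for two of the three constructs. Section 2.8.1 ties perceived behavioural control partly to having the necessary opportunities and resources. Table 1 tracks it partly by whether the facility has a paediatric sphygmomanometer. Table 1 works on subjective norms through opinion leaders, posters and feedback sessions, and section 3.3.7 places the opinion leader in the facility. Section 2.7.2 names practice culture and organisational constraints as influences on adherence.

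What is at stake is Objective 1, the factors that influence adherence. Confidence intervals would be too narrow, and a construct shared within facilities could look predictive too often. There is also a practical point. If facility is not recorded on an anonymous form, no later analysis can make the adjustment.

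**Working it through.** **1. Reproduce the plan's figure.** Inputs from 3.2.6 c: k = 7 predictors, effect size 0.15, power 80%, alpha 0.05. The overall F test uses noncentrality n × f² with k and n − k − 1 degrees of freedom. Reading 0.15 as R² gives f² = 0.15/0.85 = 0.176. Power is then 80.2% at n = 89, so the 89 reproduces, on the assumption of independent respondents. (Read as f², 0.15 would need 103; that is a separate matter.) Invitations: 89/0.5 = 178, consistent with at least 180.

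**2. Respondents per facility, if evenly spread.** 89/20 = 4.45 at 50% response. 180/20 = 9 if everyone invited answers.

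**3. Formula.** The variance inflation of a slope from unadjusted regression is

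DE = 1 + (m − 1) × ICC_y × ICC_x

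Here m is respondents per facility, ICC_y is the within-facility correlation of intention given the predictors, and ICC_x is that of the predictor. The standard error should be √DE times the reported one. The true two-sided error rate of a nominal 5% test is about 2 × [1 − Φ(1.96/√DE)].

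**4. ICCs.** The protocol gives none for staff, so all values below are assumptions shown as a range.

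| ICC_y | ICC_x | DE, m = 4.5 | SE too small by | Error rate | DE, m = 9 | Error rate |
|---|---|---|---|---|---|---|
| 0.05 | 0.05 | 1.009 | 0.4% | 5.1% | 1.02 | 5.2% |
| 0.10 | 0.10 | 1.035 | 1.7% | 5.4% | 1.08 | 5.9% |
| 0.10 | 0.30 | 1.105 | 4.9% | 6.2% | 1.24 | 7.8% |
| 0.20 | 0.30 | 1.21 | 9.1% | 7.5% | 1.48 | 10.7% |
| 0.20 | 0.50 | 1.35 | 13.9% | 9.2% | 1.80 | 14.4% |

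Worked example, fourth row, m = 4.5: DE = 1 + 3.5 × 0.2 × 0.3 = 1.21; √1.21 = 1.10; 1.96/1.10 = 1.78; two-sided tail 7.5%.

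**5. Simulation check (20 facilities, unadjusted regression).** At 4 to 5 per facility, the error rate is about 5-6% at ICCs of 0.05-0.10, 6-8% at intention ICC 0.1-0.2 with predictor ICC 0.3, and about 8-9% at 0.2 and 0.5. At 9 per facility, for the last two rows, runs gave about 10% to 16%, depending on the set-up; the formula's 10.7% and 14.4% lie inside that range. A facility random intercept with its variance estimated from the data brought the rate to about 4-7%.

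**The case against.** The case against has real weight, and several parts of it stand.

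- **The scores are individual.** Section 2.8.1 defines subjective norm as a personal perception and includes self-efficacy in perceived control. A reader might infer that these predictors are largely facility attributes. The protocol supports only that they may be partly shared.
- **The effect may be negligible.** The only ICC in the document is 0.05, and it is for adolescents. With an ICC of that size for intention and a predictor ICC of 0.05 to 0.20, standard errors are 0.4% to 1.7% too small and the error rate is 5.1% to 5.4%. Reaching 8-9% needs values with no source in the protocol.
- **A more alarming figure is available but does not apply.** For a predictor constant within facility, at intention ICC 0.2, the error rate would be about 13-14%. Section 3.2.6 f lists no such predictor.
- **The package does not hang on p-values.** Section 1.7 says findings will help develop an intervention, which might suggest that significant predictors choose its components. But section 3.3.7 and Table 1 already set out the package under all three constructs, and no rule links a test result to a component.
- **The variance estimator could be named in an analysis plan that is not shown.** That is fair for the model. It does not cover data capture: an analysis plan cannot restore a facility identifier that the form never collected. Drop boxes would let paper returns be separated by facility, and the eight demographic items in section 3.2.4 are not listed, so facility may yet be among them. Nothing says that the online form will ask for it.

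What remains is that the sampling is nested, the stated analysis and sample size ignore this, and the error can only go one way when both correlations are positive.

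**Conclusion.** The point holds at modest size. The stated regression takes no account of the facility sampling and will understate standard errors for any TPB score partly shared within a facility. Under the assumed ICCs, the true error rate at the planned response is between about 5% and 9%. It grows with response, because more respondents per facility means a larger design effect. At 9 per facility with intention ICC 0.2, it is about 11-16% for predictor ICCs of 0.3 and 0.5.

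These figures rest on assumed staff ICCs and an even spread of respondents over 20 facilities. The document cannot show which row of the table applies, so it would be wrong to conclude that the survey's results will be materially misleading.

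The consequence is confined to Objective 1. The survey is non-randomised, and the comparison between trial arms does not use it. The change is still worth making because it is standard and nearly free, and because the recording of facility has to be settled before questionnaires go out.

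**What to change.** 1. **Section 3.2.6 f:** fit the regression of intention on the TPB constructs with a random intercept for facility, by restricted maximum likelihood with small-sample degrees of freedom (in Stata, `mixed` with `reml` and `dfmethod(kroger)`). Facility-clustered standard errors with a small-cluster correction for 20 clusters are an acceptable alternative. The simulation tested a random intercept with estimated variance; this particular degrees-of-freedom option was not checked separately.
2. **Section 3.2.6 d and e:** pre-print a facility code on every paper pack and add a required facility item to the online form, before data collection starts. A facility code does not name the respondent, so the survey can remain anonymous.
3. **Reporting:** give the estimated facility ICC of intention, so that readers can see how much clustering there was.

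The cost is one model term, one code and one form item. No extra respondents are needed to fit the model. Some confidence intervals will be slightly wider.

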## **3.3 Experimental Component**

This study component will assess the effect of a multi-component theory of planned behaviour-based intervention on healthcare worker adherence to the guidelines for screening and management of hypertension among children and adolescents.

### **3.3.1 Study Design**

This will be a multi-facility, two-arm cluster-randomized study and will follow the CONSORT guidelines for the conduct of cluster randomized studies(CONSORT, 2010). There will be random allocation by clusters (health facilities) to the control and intervention arms of the study.

### **3.3.2 Study Settings**

The study will be conducted in antiretroviral therapy facilities in the Greater Accra Region. Facilities with a minimum of 40 adolescent clients on treatment as of December 2021 will be eligible for inclusion. However, facilities that do not consent to participate and those participating in other studies involving the ART staff or the adolescents living with HIV will not be included.

### **3.3.3 Participants**

The primary beneficiaries of the study are the health workers in the prospective facilities. The secondary beneficiaries are the adolescents living with HIV who assess antiretroviral care in these facilities. The beneficiary population to be included in the study are described below:

1. **Healthcare workers**

Registered clinical staff in consenting health facilities with valid licenses from relevant regulatory bodies in Ghana will be eligible for inclusion in the study. They may include prescribers, Pharmacy staff, Nurses and midwives. They will, however, be excluded if

- Less than 18 years of age
- They do not provide antiretroviral services to clients or work at the outpatient clinic
- Their practical post qualification experience in providing client care is less than one year.
- They are not available throughout the study period
- They do not agree to participate in the study by signing a consent form.

1. **Adolescents living with HIV**

Adolescents living with HIV who are clients in the study facilities will all be eligible for inclusion in the study. They will, however, be excluded if

1. They have any stage 3 or 4 HIV defining conditions
2. They started antiretroviral medications less than six months prior to the study enrolment
3. They have been diagnosed with mental illness or have a cognitive deficit
4. They are participating in another experimental study
5. There is a lack of parental or participant consent or participant assent to participate in the study.

### **3.3.4 Recruitment**

Recruitment into the study will be done at three levels: health facilities, health workers and adolescents living with HIV.

1. **Health facility recruitment**

The PI will invite potential participating clusters (i.e. health facilities) through their respective administrators to participate. In each consenting facility, the PI will identify a primary contact person for the research team.

1. **Clinical staff recruitment**

Once facilities are recruited, the PI will contact the focal persons to obtain details of potential clinical staff who may be interested in participation based on the inclusion and exclusion criteria. The potential participants will be engaged to discuss the study protocol. Those who express interest will be provided with a study invitation pack, including a letter of invitation, information sheet and consent form.

1. **Patient recruitment**

Using a random sequence provided by the study team, a random sample of 20 adolescents living with HIV per facility will be selected for baseline and end-line assessment. The consent of their caregivers will be sought, followed by the adolescents’ consent or assent as may be age-appropriate.

### **3.3.5 Sample size**

This study is designed to detect a doubling (100%) of the proportion of adolescent visits that had BP screening done (conservatively calculated in STATA version 16 as an increase from 17% to 34%) between the intervention and control groups. It is based on the assumption of a 2-sided test with 80% power at a 5% significant level, cluster sizes of 20 adolescents and an intra-cluster correlation coefficient (ICC) of 0.05. Accordingly, two groups of ten (10) health facilities will be needed at the minimum. As this sample size estimation does not account for any potential loss to follow-up, we will recruit additional two facilities per arm (24 in total). Thus, a total of about 96 health workers (4 per facility) and about 480 adolescents living with HIV (20 per facility) will be enrolled in this study.

### **3.3.6 Randomization**

**a. Sequence generation:** The unit of randomization will be the health facility. Randomization will be performed by a statistician independent of the study team, using computer-generated random permuted blocks and will be stratified by type of health facility (regional, district/ municipal, Polyclinic, Health Centre). Twelve facilities will be in the intervention arm and the rest in the control arm. The study statistician will provide each facility with a computer-generated list of random numbers to select a sample of 20 adolescent clients to participate in the baseline and end-line survey.

**b. Allocation concealment**: Each facility will eventually become aware of its allocation, but allocation will be concealed until the baseline assessment is completed. Adolescents will not be allocated to alternative interventions within a facility, so allocation concealment will not be an issue.

**c. Implementation of clusters:** The PI will provide the list of prospective facilities by type to the study statistician, anonymized by an ID**.** The study statistician will generate the random sequence and allocate practices to two separate dummy-coded groups without knowing which group will receive the intervention; the study statistician will remain blind to allocation until the collected follow-up data. Random allocation of clusters to intervention or control will occur consecutively as practices are recruited until the target sample size (24) is reached.

**d. Blinding:** Given the nature of the intervention, healthcare workers will inevitably be aware of their allocation and thus, blinding participants will not be possible. Each facility will also become aware of allocation. However, facilities will not be informed of allocation until after both facilities and individual health workers are identified and recruited (i.e., not until after baseline assessment). Adolescents within each facility will remain blind to allocation. The outcome assessors will be kept blind to the allocation. The facility contact that will use the random sequence of numbers to identify the sample of 20 patients within each facility will possibly not be blind to allocation. Blinding the entire research team is also impossible as intervention facilities will be contacted to arrange the sessions. However, the study statistician conducting the outcome analysis will remain blinded to allocation until after the outcome data have been collected at follow-up.

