### **3.3.9 Outcomes**

#### **a. Primary outcomes**

The primary outcome will be the effect of the intervention on healthcare workers’ adherence to the guideline. It will assess adherence to recommendations on the

1. frequency of screening
2. Detection of elevated or high BP,
3. Investigation of high BP and
4. Management of elevated or high BP.

These will be assessed using a data extraction tool based on the HIV client care booklet. The tool will extract the data from the client care records of adolescents who received care within the period of interest. At baseline, it will assess the records of 20 randomly selected adolescents who received care at the facility six months prior to the assessment and extract the data from their most recent visit. At follow up, data will be extracted from the most recent visit of 20 randomly selected adolescents who received care at the facility after the intervention commenced.

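### The protocol does not settle whether the follow-up records come from the baseline 20 adolescents or a new 20, and a new draw could be made by a facility contact who knows the allocation

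*Protocol*

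**What the plan says.** **One sample.** Section 3.3.4 says that "a random sample of 20 adolescents living with HIV per facility will be selected for baseline and end-line assessment". Section 3.3.6 a likewise has the statistician supply each facility with one list of random numbers, to select 20 clients for the survey at both time points. Section 3.3.5 fits this reading: it enrols about 480 adolescents (24 × 20) and adds two facilities per arm because of possible loss to follow-up. The data extraction form also has fields for weight at baseline and at end-line on one record.

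**Two frames.** Section 3.3.9 a defines the primary outcome. Its baseline records belong to 20 randomly selected adolescents seen in the six months before the assessment. Then: "At follow up, data will be extracted from the most recent visit of 20 randomly selected adolescents who received care at the facility after" commencement of the intervention. Section 3.3.9 b, on the survey and physiological measurements, can be read either way.

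**Who selects, and when.** Section 3.3.6 b conceals allocation until the baseline assessment is complete. It then says: "Adolescents will not be allocated to alternative interventions within a facility, so allocation concealment will not be an issue". Section 3.3.6 d states that the facility contact who uses the random numbers to "identify the sample of 20 patients within each facility will possibly not be blind to allocation". The same section keeps outcome assessors and the analysing statistician blind.

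**The concern.** In a cluster trial, concealment within a facility is not the only question. What also matters is whether the people whose data are read are chosen after the facility's arm is known. Section 3.3.6 b gives the absence of within-facility allocation as its reason for setting concealment aside, yet section 3.3.6 d allows that the person identifying the 20 may be unblinded.

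The primary outcome rests on 20 records per facility. If someone who knows the arm can influence which clients enter that list, or who replaces an unavailable client, the arms can differ without any change in facility practice. Because the sections disagree on whether the 20 are retained or redrawn, two field teams could both comply and run different designs with different exposure to this risk.

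**Working it through.** **Step 1. The two readings**

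| | Baseline 20 retained (3.3.4, 3.3.6 a) | New 20 at follow-up (3.3.9 a) |
|---|---|---|
| When selected | before disclosure | after disclosure |
| Arm known to the selector | no | possibly, if the facility contact selects |
| What remains open | the facility may know whose records will be read | how the list is built and how clients are replaced |

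Section 3.3.9 a names no one as selecting the records. Section 3.3.6 is the only place that says who identifies a sample of 20, and part a ties that list to the survey. The link to the primary outcome is therefore inferred.

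**Step 2. The plan's own figure**

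Inputs, all from section 3.3.5: "2-sided test with 80% power at a 5% significant level"; rates "conservatively calculated in STATA version 16 as an increase from 17% to 34" per cent; "cluster sizes of 20 adolescents and an intra-cluster correlation coefficient (ICC) of 0.05".

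- Design effect: 1 + (20 − 1) × 0.05 = 1.95.
- Individuals per arm without clustering, pooled two-proportion formula: n = [1.96 × √(2 × 0.255 × 0.745) + 0.842 × √(0.17 × 0.83 + 0.34 × 0.66)]² / 0.17², rounded up to 103.
- With clustering: 103 × 1.95 = 200.9, against 10 × 20 = 200 in the plan. Power at 200 per arm (effective n = 200 / 1.95 = 102.6) is 80.2%.
- The unpooled formula gives 99.3 × 1.95 / 20 = 9.68, rounded up to 10.

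The stated "two groups of ten (10) health facilities will be needed at the minimum" reproduces. The sample size is not in question.

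**Step 3. How much distortion would matter**

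Assume no true effect and a BP-check rate p in both arms. In every intervention facility, a share s of the 20 follow-up records is replaced by records that have a BP entry. The documents give no value for s; it is an assumption.

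- Apparent rate = (1 − s) × p + s, so the spurious difference is s × (1 − p).
- Effective n with 12 facilities per arm: 240 / 1.95 = 123.1.
- Chance of a significant result in favour of the intervention: Φ{[d√n − 1.96√(2p̄(1 − p̄))] / √(p₁(1 − p₁) + p₂(1 − p₂))}. Here d is the spurious difference, n the effective n, p₁ and p₂ the true and apparent rates, and p̄ their mean.

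| Records swapped of 20 | p = 17%: apparent rate | false significance | p = 34%: apparent rate | false significance |
|---|---|---|---|---|
| 1 | 21.15% | 13% | 37.3% | 8% |
| 2 | 25.3% | 36% | 40.6% | 19% |
| 3 | 29.45% | 64% | 43.9% | 36% |
| 4 | 33.6% | 85% | 47.2% | 56% |

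At p = 17%, two swaps add 0.10 × 0.83 = 8.3 points. Mimicking the full planned effect needs s = 0.17 / 0.83 = 0.205, or 4.1 of 20 records. The simple product 0.17 × 20 = 3.4 only restates the powered effect as a net gain in records. It ignores that some swapped-out records already had a BP entry.

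**Step 4. Would a new draw be separate from the baseline 20?**

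Section 3.3.2 admits facilities with 40 adolescents. An independent draw of 20 from 40 shares on average 20 × 20 / 40 = 10 with the first draw. In the smallest facilities, redrawing does not give a separate sample.

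**The case against.** **Safeguards exist.** The random numbers come from the statistician, outcome assessors are blind, and applying a supplied list is not free choice. The protocol also discloses the limitation itself. This stands as a reduction of risk. It does not cover how the facility builds the list to which the numbers are applied, or who replaces a client. A blind extractor reads accurately whichever folders are handed over.

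**A reader might infer that both readings are biased as planned.** The documents do not support that. A retained 20 would be chosen before disclosure, so an unblinded selector is largely ruled out. The research office BP, ambulatory BP and arterial stiffness measurements take place in both arms, so they do not by themselves create a difference between arms. A narrower point remains. A facility that identified its own 20 may know whose records will be read, and intervention facilities, which receive audit, feedback and opinion-leader support (section 3.3.7 and Table 1), may have more reason to prompt BP checks in those clients.

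**A reader might take it as stated that the contact picks the primary-outcome records.** It is not. The objection is right that the list in section 3.3.6 a serves the survey, which section 3.3.9 b places under secondary outcomes. Section 3.3.9 b also says the survey validates the extracted records, so overlap is plausible but not specified.

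**A reader might add that consent after disclosure biases the BP-check rate.** Section 3.3.4 seeks consent after selection, and section 3.3.3 excludes adolescents without it. But section 3.6 covers record extraction by permission from the heads of medical records. Whether consent filters the primary-outcome records is unclear, so this cannot be claimed.

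**It might be said that a statistical analysis plan would settle this.** Who selects participants, when, and whether they are the same people is trial conduct. The protocol already addresses it, inconsistently.

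**Conclusion.** The point holds in conditional form. The contradiction over the follow-up sample is in the text. If a new 20 is drawn, the facility already knows its arm, and the only selector the protocol names may know it too. The sentence dismissing concealment does not hold for a draw made after disclosure. If the baseline 20 are kept, the selection risk largely goes and only possible prompting within a known list remains.

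The documents show that the BP-check rate is open to bias, not that it will be biased. The illustrative sizes, about +8 points for 2 swapped records of 20 and the whole 17-point effect for about 4, assume no true effect, a 17% rate and the same swap in all 12 intervention facilities. They show sensitivity and do not estimate how often this would happen. The matter should be resolved before the follow-up draw.

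**What to change.** 1. Align sections 3.3.4, 3.3.5, 3.3.6 and 3.3.9 a and b on whether each outcome uses the baseline 20 or a new draw.
2. For the primary outcome, keep the frame of section 3.3.9 a (attendees since the intervention began). Have each facility export a complete, date-locked list of eligible attendees. The blinded statistician draws 20 IDs and an ordered replacement list and gives them directly to the blinded extractors on the extraction day. Every replacement is logged with its reason.
3. For the physiological outcomes, state whether the adolescents recruited before disclosure are the ones re-measured at six months.
4. Delete the sentence that concealment is not an issue, or correct it to say how selection after disclosure is protected.

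The cost is a register export from each of the 24 facilities and wording changes. The number of records stays at 20 per facility per time point. The downside is that the record sample and the survey sample overlap less, so the survey validates fewer extracted records. In facilities near the 40-client minimum about half may still overlap by chance, so the draw should not be described as separate from the baseline 20.
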